### Statistical analysis

For the graphic description of the flow of the participants throughout the protocol, the CONSORT diagram is used. The intention-to-treat (ITT) method will also be used. In the treatment of the missing values, it will be checked if the loss of data occurs completely at random using Little’s MCAR test, and then, the estimation of the missing values will follow the maximum likelihood method through the EM algorithm [73].

As a step prior to determining the effectiveness of the intervention programs, the homogeneity of the groups will be analysed, taking into account all the variables evaluated and using *χ*^2^ tests and ANOVAs according to the type of variables.

To determine if the treatment is better than the control group, one-factor (type of intervention) ANOVAs and ANCOVAs will be performed for each of the scores in the posttreatment (or second pre measure for the control group on the waiting list) of the continuous treatment outcome variables, using in the ANCOVAs the value of the pretreatment evaluation as covariance. In the case of ANOVAs, the DSM or Games-Howel tests will be used for post hoc analyses depending on whether the assumption of equality of variances is met. In the case of significant differences in the ANCOVAs, the groups will be analysed in pairs using new ANCOVAs. For those variables that do not adjust to normality, the corresponding nonparametric tests will be applied (i.e. Kruskal–Wallis and Mann–Whitney *U* for pairwise comparisons). For the qualitative variables, *χ*^2^tests will be used.

To determine the changes over time, the two basic moments will be analysed first (i.e. the changes from pretreatment to posttreatment or the second premeasure for the control group). Repeated-measures ANOVAs will be performed in a mixed design with an intergroup factor with three levels (the two treatments plus the control group) and an intrasubject factor (pre and post measures). In those variables that do not adjust to normality, the corresponding nonparametric tests will be applied (i.e. Friedman). Additionally, in this case, for the qualitative variables, *χ*^2^ tests will be used.

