In a second moment of the analysis of the changes over time, the changes between the pre, post and follow-ups will be analysed only for the two experimental groups. For this, an ANOVA will be applied for each of the outcome variables, including an intergroup factor (with two levels: CBT and CBT-M +) and an intrasubject or repeated measures factor, with five levels (i.e. pre, post, 3 months, 6 months and 12 months). In the application of these ANOVAs, the assumption of sphericity will be verified using the Mauchly test, and where appropriate, the Huynh-Feldt correction will be used. Likewise, ANCOVAs of one factor (type of treatment) will be performed for each outcome variable, using the value of the pretreatment evaluation as covariance.

To determine the differences between the two treatments, the intergroup differences and the interactions between time and type of treatment obtained in the different ANOVAs and ANCOVAs mentioned in the previous point will be addressed.

In all analyses, the Holm–Bonferroni correction will be used to adjust the level of significance for multiple comparisons.

To establish the clinical significance of the changes obtained, *χ*^2^ tests will be used considering the data relative to those variables that present a cut-off point capable of discriminating the clinical improvement of the participants. Likewise, the relative risk of presenting problems of one experimental group with respect to the other at different times of measurement will be calculated. In addition, the McNemar related proportions will be calculated to verify if the percentage of problems is the same or different in the pretreatment and in the different subsequent measurement moments, and the Jacobson-Truax method will be applied by calculating the index of reliable change. This analysis will be supplemented by the calculation of the effect size of each variable.

In the specific analysis of the reabuse or revictimization variables, it is expected that the scores show high asymmetry and kurtosis, so they will be recoded as dichotomous variables (presence vs. absence for each type of violence or abuse) in accordance with the procedure described by Johnson et al. [12].

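### Pre-to-post change in qualitative outcomes is assigned to χ² tests, which under their two usual readings do not test change in paired data

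*Protocol article*

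**What the plan says.** All of this is in the Protocol article, Statistical analysis.

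- **Arms at posttreatment.** An earlier paragraph compares the groups after treatment and gives χ² tests to the qualitative variables. That is a comparison of different women at one time point.
- **Change over time.** The next paragraph opens: "To determine the changes over time, the two basic moments will be analysed first". It defines these as "the changes from pretreatment to posttreatment or the second premeasure for the control group". Continuous variables get within-subject methods: a mixed repeated-measures ANOVA, or Friedman if non-normal. For the rest: "Additionally, in this case, for the qualitative variables, *χ*^2^ tests will be used". No table or paired variant is specified.
- **Clinical significance.** A later paragraph applies χ² to "those variables that present a cut-off point capable of discriminating the clinical improvement of the participants", and adds that "the McNemar related proportions will be calculated to verify if the percentage of problems is the same or different in the pretreatment" and at the later measurements.
- **Reabuse.** The paragraph after that expects skewed scores, "so they will be recoded as dichotomous variables (presence vs. absence for each type of violence or abuse". It names no test.

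**The concern.** The question in the change paragraph is whether a woman's status differs between two occasions, so the two columns of data are paired. A Pearson χ² can be set up on such data in two usual ways, and each tests something else.

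1. **Pre-by-post table within an arm.** The null hypothesis is that later status is unrelated to earlier status. The test rejects when status persists, whether or not the percentage has moved.
2. **Occasion-by-status table within an arm.** The null hypothesis of equal percentages is right, but the standard error assumes two independent samples. With positive pre–post correlation that standard error is too large.

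The McNemar sentence does not settle the matter. It stands in the paragraph on variables with a cut-off. Reabuse is dichotomised afterwards with no test attached, so only the general χ² rule clearly reaches it. For cut-off variables, the two paragraphs name different tests for one pre/post question. The Discussion singles out the effect on revictimization as a strength of the trial, so this outcome should have a test that fits its question.

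**Working it through.** **Inputs from the plan.** Sample size section: alpha 0.05, power 0.80, effect size from 0.71, at least 31 per group, 30% dropout, 45 per group, 135 in total. Sidedness is not stated; I take two-sided.

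**The plan's own figures.** n per group = 2(1.96 + 0.84)²/0.71² ≈ 31.1; 31/(1 − 0.30) = 44.3, rounded up to 45; 3 × 45 = 135. These reproduce. They concern a continuous outcome. The article gives no power, base rate, expected change or pre–post correlation for any qualitative variable, so the percentages and phi below are **assumptions**. I use n = 31 and n = 45 as the range of women per arm.

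**Set-up.** With pre rate p, post rate q and correlation phi:

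- P(positive both times) = pq + phi·√[p(1−p)q(1−q)].
- Cells: a = positive at both; b = pre only; d = post only; e = neither.
- Pre-by-post χ² = n(ae − bd)²/[(a+b)(d+e)(a+d)(b+e)], centred near n·phi².
- Unpaired χ² = (p̂ − q̂)²/[2p̄(1−p̄)/n], where p̄ is the mean of p̂ and q̂.
- McNemar χ² = (b − d)²/(b + d). The exact version is binomial(b + d, ½).

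**Hand check, reading 1.** At phi 0.5, n·phi² = 31 × 0.25 = 7.75 and 45 × 0.25 = 11.25, against a critical value of 3.84. Frequent rejection is expected with no change.

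**Hand check, reading 2.** For 60% to 40% at phi 0.5, P(both) = 0.24 + 0.5 × 0.24 = 0.36, so P(pre only) = 0.24 and P(post only) = 0.04. At n = 45 the noncentrality is about 45 × 0.2²/0.28 = 6.4 for McNemar and 45 × 0.2²/0.5 = 3.6 for the unpaired χ².

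**Rejection with no change (50% at both times), summing over all possible tables:**

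| n | phi | pre-by-post χ² | unpaired χ² | asymptotic McNemar |
|---|---|---|---|---|
| 31 | 0.2 | 21% | 3.2% | 4.4% |
| 31 | 0.3 | 41% | 2.2% | 4.3% |
| 31 | 0.5 | 83.5% | 0.7% | 4.5% |
| 45 | 0.2 | 26% | 2.5% | 5.1% |
| 45 | 0.3 | 51% | 1.7% | 4.8% |
| 45 | 0.5 | 93.5% | 0.5% | 4.3% |

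**Power for a fall from 60% to 40%:**

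| n | phi | unpaired χ² | asymptotic McNemar | exact McNemar | loss vs asymptotic | loss vs exact |
|---|---|---|---|---|---|---|
| 31 | 0 | 37% | 34% | 26% | −3 | −11 |
| 31 | 0.3 | 34% | 43% | 34% | 9 | 0 |
| 31 | 0.5 | 31% | 58% | 45% | 27 | 14 |
| 45 | 0 | 46% | 48% | 38% | 2 | −8 |
| 45 | 0.3 | 45% | 62% | 53% | 16 | 7 |
| 45 | 0.5 | 44% | 76% | 68% | 32 | 24 |

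For a large change (80% to 40%, n = 45) the loss is under 1 point. If every woman is positive at entry, the pre-by-post χ² cannot be computed and the unpaired test loses essentially nothing. Holm–Bonferroni is not applied in these tables; it would lower all the rejection rates.

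**The case against.** **The sentence may mean something valid.** It does not say which table is tested, and the paragraph describes a design with three groups. A χ² comparing change categories (for example improved, unchanged, worse) across arms would be valid. This stands, so it cannot be said that the analysis will go wrong. But no such categories are defined. McNemar's statistic is also referred to a χ² distribution, so a generous reader might include it; yet the section names McNemar separately where it means it.

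**The paired test is already planned.** This stands for cut-off variables: a reader who inferred that the plan has no paired test would be mistaken. One can argue that "the McNemar related proportions will be calculated to verify if the percentage of problems is the same or different" is not limited by the paragraph's first sentence. Its setting is still clinical significance and cut-offs, so reabuse is not clearly covered.

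**The arm comparison exists.** The posttreatment χ² between arms is a valid test in a randomised trial. This stands. Baseline adjustment adds efficiency and an arm-by-time comparison parallel to the mixed ANOVA; it does not repair an invalid test.

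**The affected outcomes are partly inferred.** The change paragraph does not mention reabuse, and its own paragraph follows a cited procedure that is not shown. The nine motivation-to-leave items may be summed to a score, in which case the sentence does not concern them.

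**The power loss is not fixed.** A reader might infer a loss of about 30 points. That needs roughly a 20-point change, phi near 0.5 and the asymptotic McNemar test. With low correlation and the exact test, the unpaired χ² has more power.

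**Conclusion.** The point holds in limited form. The plan attaches χ² tests to a question about within-woman change. Under the two usual readings they either test association or ignore the pairing. The first defect is the more serious: with no change, rejection is about 41–51% at phi 0.3 and 84–93% at phi 0.5, and already 21–26% at phi 0.2. The second makes the test conservative (about 0.5–0.7% under no change at phi 0.5), with a power effect that runs from a small gain to a loss of about 32 points over the settings tabulated. All these figures rest on assumed rates and correlations at a two-sided, unadjusted 5% level.

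Two stronger conclusions are not supported. The documents do not show that change would be declared falsely in most analyses, because the table and phi are unknown. Nor is the main result at risk: the continuous primary PTSD score is analysed by ANCOVA and repeated-measures ANOVA and is unaffected. The exposure is limited to dichotomous outcomes, chiefly reabuse, and to the unreconciled instructions for cut-off variables. It should be corrected before analysis.

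**What to change.** In the changes-over-time paragraph of Statistical analysis:

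- Replace χ² with McNemar's test (asymptotic or mid-p; exact when discordant pairs are few) for within-arm change in all dichotomous outcomes, naming reabuse, and align this with the clinical-significance paragraph.
- Compare arms with a logistic regression of posttreatment status on arm, adjusted for pretreatment status, or a GEE logistic model with arm-by-time. Use a penalised or exact fit if events are few.
- Keep χ² for comparing arms at a single time point.
- Where every woman is positive at entry, as may be so for PTSD diagnosis given the eligibility criteria, use only the between-arm posttreatment comparison.

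The cost is analysis-plan wording; no new data are needed. The drawbacks are the special fitting needed with sparse events and the lower power of the exact McNemar test when pre–post correlation is weak. The reason for the change is that the test should match its question; a gain in power is not guaranteed.

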### Sample size

To determine the target sample size, we considered the effect sizes found in the literature (specifically, the overall effect size—omnibus—calculated in the meta-analysis by Arroyo et al. [5]), which ranges from 0.71 to 1.33. Considering an alpha of 0.05 and a statistical power level of 0.80, a minimum group size of 31 was established. Taking a conservative estimate of the expected dropout rate of 30%, a sample size of 45 women per group will be the target, indicating a total of 135 participants across the 3 experimental conditions (CBT, CBT-M + and WL control group).

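### The rule for CBT-M+ versus CBT admits a between-group main effect that is diluted by the pretreatment score, and does not say which of several analyses decides

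*Protocol article*

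**What the plan says.** The Statistical analysis section of the protocol article plans several analyses of the same outcomes.

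- At posttreatment, each continuous outcome gets a one-factor ANOVA and an ANCOVA with the pretreatment score as covariate.
- For change from pre to post: "Repeated-measures ANOVAs will be performed in a mixed design with an intergroup factor with three levels". The two factors are "an intergroup factor with three levels (the two treatments plus the control group) and an intrasubject factor (pre and post measures").
- For follow-up, CBT and CBT-M+ are compared in an ANOVA whose repeated factor is defined as "with five levels (i.e. pre, post, 3 months, 6 months and 12 months"), with one-factor ANCOVAs adjusted for pretreatment alongside.

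The difference between the two treatments is then to be judged from "the intergroup differences and the interactions between time and type of treatment obtained in the different ANOVAs and ANCOVAs". Holm–Bonferroni is to be applied in all analyses for multiple comparisons; the family of tests is not defined. No analysis is ranked above another.

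**The concern.** In a mixed ANOVA, the between-group factor compares arm means averaged over every level of time. When pretreatment is one of those levels, the average includes a visit that treatment cannot have influenced. The main effect then estimates only part of the treatment effect, and any chance imbalance at pretreatment enters the estimate with the weight of that level. The test keeps its 5% error rate under no effect, but as an estimate of the treatment effect it is biased towards zero.

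The rule places this quantity on a level with the ANCOVA, the posttreatment ANOVA and the group-by-time interaction. These can disagree, and the text gives no way to settle a disagreement. At stake is the comparison that the Abstract gives as the study's aim: whether adding the positive memory module helps.

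**Working it through.** **Inputs from the documents (Sample size section).** "Considering an alpha of 0.05 and a statistical power level of 0.80, a minimum group size of 31 was established"; effect size, "which ranges from 0.71 to 1.33"; "Taking a conservative estimate of the expected dropout rate of 30%, a sample size of 45 women per group will be the target".

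**Assumed, not in the documents.** Two-sided alpha; equal variances (SD = 1); the same correlation r between any two visits (compound symmetry), with r = 0.3, 0.5 and 0.7; an effect d that is constant at all four later visits for the five-level analysis.

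**Step 1: the plan's own figure.** With d = 0.71, the normal approximation gives n = 2 × ((1.960 + 0.842)/0.71)² = 31.1 per group, and the t-based value is 32.1. The stated 31 is therefore a two-group calculation at the lower end of the effect range. Then 31/0.70 = 44.3, rounded up to 45, and 3 × 45 = 135. The sample size reproduces and is not in dispute.

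**Step 2: what the main effect estimates.** With k equally weighted levels, one of them pretreatment, the expected arm difference is d(k − 1)/k.

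- Pre/post, k = 2: 0.71 × 1/2 = 0.355.
- Five levels, k = 5: 0.71 × 4/5 = 0.568.

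**Step 3: standardised effect of each test, CBT-M+ against CBT.**

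- Posttreatment ANOVA: d
- Posttreatment ANCOVA: d/√(1 − r²)
- Pre/post interaction: d/√(2(1 − r))
- Pre/post main effect: (d/2)/√((1 + r)/2)
- Five-level main effect: 0.8d/√((1 + 4r)/5)
- Baseline-adjusted mean of the four later visits: d/√((1 + 3r)/4 − r²)

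Example at r = 0.5: the pre/post main effect is 0.355/√0.75 = 0.41; the ANCOVA is 0.71/√0.75 = 0.82.

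**Step 4: power at 31 per arm, d = 0.71, two-sample t-test, alpha 0.05.**

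| Test | r = 0.3 | r = 0.5 | r = 0.7 |
|---|---|---|---|
| Pre/post main effect | 0.40 | 0.36 | 0.32 |
| Posttreatment ANOVA | 0.79 | 0.79 | 0.79 |
| Pre/post interaction | 0.64 | 0.79 | 0.94 |
| Posttreatment ANCOVA | 0.82 | 0.89 | 0.97 |
| Five-level main effect | 0.91 | 0.81 | 0.71 |
| Adjusted mean of four later visits | 0.99 | 0.99 | >0.99 |

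The first four rows use pre and post only. The last two use all visits and should be compared with each other. These are pairwise figures; the planned pre/post ANOVA has three groups, so its own main effect is an omnibus test with 2 degrees of freedom.

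**Step 5: four parallel pre/post tests under no effect.** Simulation of one two-arm contrast (20,000 runs per setting, 31 and 45 per arm, r = 0.3 to 0.7), testing the posttreatment ANOVA, ANCOVA, interaction and main effect. Each rejects in about 5% of runs. At least one rejects in about 11–12% without correction. If Holm–Bonferroni spans all four, so that the smallest p-value must fall below 0.05/4 = 0.0125, the figure is about 3%. The price is power: at r = 0.5, an ANCOVA that must pass 0.0125 has power 0.74 instead of 0.89.

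**The case against.** The strongest reply is that the sentence need not mean the mixed-ANOVA main effect at all. The planned ANCOVAs have one factor and cannot yield a time interaction, so the sentence must be read at least partly distributively. One could take group differences from the one-factor analyses and interactions from the mixed ANOVAs, and then the diluted test plays no part. This stands as a possible reading. But the wording covers the group differences of all the ANOVAs, so it admits the main effect without prescribing it.

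Four stronger inferences are tempting, and the documents do not support them.

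- *The effect is halved.* That is true only of the pre/post ANOVA. In the five-level ANOVA, the one confined to the two treatments, the loss is one fifth under a sustained effect. The interactions and ANCOVAs named in the same sentence are not diluted.
- *The planned pre/post test has power 0.36.* That figure is for a pairwise contrast at r = 0.5, not for the three-group omnibus test.
- *The error rate is more than doubled.* This holds only if Holm–Bonferroni does not span the parallel tests, and its family is left open.
- *The comparison is already underpowered.* The document gives no basis for this. At its own planning effect the posttreatment ANOVA has 0.79 and the ANCOVA more.

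The posttreatment ANOVA and the interaction are also legitimate tests: both are unbiased under randomisation, and the case for ANCOVA over them is one of efficiency only.

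Finally, a condensed article may leave the choice of deciding test to an analysis plan. That answers mere silence. It does not answer a published rule that counts a diluted quantity as equal evidence.

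**Conclusion.** The point holds as a defect in the stated rule. It lets a main effect biased towards zero count as evidence on CBT-M+ versus CBT, beside a stronger analysis that is already planned, and it does not say which prevails. The dilution (d/2, or 4d/5 if the effect is sustained) is algebra and does not depend on r. The power figures rest on d = 0.71, 31 per arm, compound symmetry and an assumed r of 0.3 to 0.7. Over that range the main effect is the weakest of the four pre/post tests and the ANCOVA the strongest. The multiplicity consequence is conditional: excess error if the Holm family leaves out the parallel tests, lost power if it includes them. The matter should be corrected before analysis; it does not call the design or the sample size into question.

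**What to change.** Amend the Statistical analysis section in four places.

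1. Name the baseline-adjusted ANCOVA of EGEP-5 severity at posttreatment as the deciding analysis for CBT-M+ versus CBT.
2. For follow-up, compare the arms on the post-baseline visits with pretreatment as covariate, through the planned ANCOVAs or a longitudinal model.
3. State that the between-group main effect of any ANOVA that includes pretreatment is not used as evidence of a treatment difference.
4. Label the posttreatment ANOVA and the interactions supportive. They then no longer need to compete with the deciding test in the Holm–Bonferroni family.

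The cost is analysis wording only. The ANCOVA is already planned, no further data or participants are needed, and there are fewer competing results to report.

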### Eligibility criteria

We adopt the WHO definition of IPV as ‘any behaviour within an intimate relationship that causes physical, psychological or sexual harm to those in the relationship’ [29]. Participants are eligible if they (1) are women; (2) are over 18 years old; (3) are proficient in the use of the Spanish language; (4) are or have been victims of IPV; (5) have experienced IPV at least one month before the start of the trial; (6) present symptoms of PTSD according to DSM-5 criteria as determined by the Global Assessment of Posttraumatic Stress Scale 5 (EGEP-5; in Spanish: Evaluación Global de Estrés Postraumático 5; Crespo et al. [30]); and (7) have voluntarily agreed to take part in the study.

Participants will be excluded if they (1) show suicide risk as assessed by item 9 (scores > 1) of the Spanish version of the Beck Depression Inventory II—BDI-II [31]; (2) present conditions that could prevent compliance with the treatment (namely, abuse of alcohol or drugs, cognitive impairment or illiteracy in Spanish); (3) have been diagnosed or suffer from psychotic disorders; and (4) have received trauma-focused treatment within the past 6 months.

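### The between-arm comparisons on clinical cut-offs leave out the pretreatment score: valid under randomisation, but less efficient than the data allow

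*Protocol article*

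**What the plan says.** All references are to the protocol article.

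- **Statistical analysis, clinical significance.** χ² tests are planned "considering the data relative to those variables that present a cut-off point capable of discriminating the clinical improvement of the participants". The same paragraph adds that "the relative risk of presenting problems of one experimental group with respect to the other at different times of measurement will be calculated". Neither sentence restricts, stratifies or adjusts by pretreatment value. The paragraph also plans McNemar tests of each later visit against pretreatment, and the Jacobson-Truax reliable change index.
- **Statistical analysis, continuous outcomes.** Arms are compared by ANOVA and ANCOVA, "using in the ANCOVAs the value of the pretreatment evaluation as covariance".
- **Eligibility criteria.** Women must "present symptoms of PTSD according to DSM-5 criteria" on the EGEP-5, which is also the primary outcome instrument. No minimum is set on the BDI-II, BAI or other secondary scales.
- **Objectives.** The clinical significance of the changes is one of the four listed efficacy assessments.
- **Sample size.** "Considering an alpha of 0.05 and a statistical power level of 0.80, a minimum group size of 31 was established", for an effect size "which ranges from 0.71 to 1.33". No power is stated for any cut-off outcome.

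**The concern.** The same scale is handled in two ways. As a continuous score it is compared between arms with the pretreatment value as covariate. Once cut into above and below, which already discards information, it is compared with no covariate at all. The missing covariate is in hand for every woman.

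Two things follow. The between-arm comparison has less power than the same data would give with adjustment. And where entry does not require the problem, being below the cut-off at a later visit covers two kinds of women: those who came down from above it, and those who were never above it. The raw proportion and the raw relative risk cannot separate them, although the stated purpose is the clinical significance of change.

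**Working it through.** **1. The plan's own figure.** With effect size 0.71, two-sided α 0.05 (sidedness is not stated) and power 0.80:

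n = 2(1.960 + 0.842)² / 0.71² = 15.70 / 0.5041 = 31.1 per group.

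This rounds up to 32 (33 by the t distribution) against 31 stated. Power at 31 is 0.798 by the normal formula and 0.785 by t. Then 31 / 0.70 = 44.3, so 45 per group, and 3 × 45 = 135. The stated size is reproduced, but for a continuous outcome. I use 31 and 45 per arm below.

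**2. Assumed inputs, none in the article.** Pre and post scores are bivariate normal with SD 1 and correlation r = 0.5-0.7. The share p above the cut-off at pretreatment is 60-90%. Both arms improve by 0.5 SD and the arms differ by a further 0.6 SD. Tests are two-sided at 0.05, with no Holm step.

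**3. Plain χ² by hand.** The cut-off is c = −Φ⁻¹(p). The share still above it is 1 − Φ(c + 0.5) in one arm and 1 − Φ(c + 1.1) in the other.

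- p = 0.60: c = −0.253, giving 0.403 v 0.199.
- p = 0.75: c = −0.674, giving 0.569 v 0.335.

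Power ≈ Φ[(difference − 1.96·SE₀) / SE₁], where SE₀ is the pooled and SE₁ the unpooled standard error. For p = 0.60 and n = 45, SE₀ = 0.0967 and SE₁ = 0.0942, so power = Φ[(0.204 − 0.189) / 0.0942] = Φ(0.15) = 0.56. For p = 0.75 and n = 31, SE₀ = 0.126 and SE₁ = 0.123, so power = Φ[(0.234 − 0.248) / 0.123] = Φ(−0.11) = 0.46. Both agree with the simulation below.

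**4. Simulated power, χ² against the likelihood-ratio test for arm in logistic regression with the continuous pretreatment score.**

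| Per arm | Above cut-off at pretreatment | χ² | Adjusted |
|---|---|---|---|
| 31 | 60-75% | 0.42-0.50 | 0.49-0.62 |
| 45 | 60-75% | 0.56-0.60 | 0.64-0.78 |

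Setting by setting, repeat runs put the gain at about 5-17 points. At 90% above the cut-off it is 7-16 points. With every woman above it, the gain is still about 3-10 points (for example 0.74 to 0.85 at n = 45, r = 0.7), because severity still varies above the cut-off.

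**5. Test size.** With no true difference, χ² rejects in about 0.04-0.06 of trials and the adjusted test in 0.046-0.064. Part of the gain may therefore be test size. The gain is for the logistic likelihood-ratio test. In a check under the same model, the robust Wald test from modified Poisson regression gained less in every setting.

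**6. Where the gain comes from.** In the same model:

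- adjusting for the continuous score gains about 5-17 points;
- adjusting only for pretreatment status (above or below) gains about 2-9;
- a χ² test only in women above the cut-off at pretreatment mostly loses power, by up to 13 points (for example 0.575 to 0.455 at n = 45, p = 0.60, r = 0.5).

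The gain is ordinary covariate efficiency. It does not come from removing women who never had the problem.

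**7. How mixed the below-cut-off group can be.** If 60-90% start above the cut-off and mean improvement is 0.7 SD, 22-55% of women below it afterwards were already below it at pretreatment.

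**The case against.** The strongest reply is that nothing here is invalid. The arms are randomised, so an unadjusted χ² test and relative risk are unbiased and keep their error rate. The efficient comparison on these scales is already planned as ANCOVA, and the cut-off analysis supplements it. The same paragraph links to pretreatment through McNemar and reliable change, and logistic regression of therapeutic success appears at the end of the section. The denominator may be defined in the full protocol.

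Much of this stands, and it makes the point minor. It does not remove it. McNemar compares visits within women, and reliable change is computed woman by woman; the text plans no baseline-adjusted between-arm test on either. The logistic regression is described as a search for variables related to success, not as the arm comparison. The two between-arm statistics are named methods, and no adjustment is stated for them.

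Four stronger readings are tempting and are not supported.

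- **Women who never had the problem are counted as treatment successes, and this causes the power loss.** The text counts women presenting problems and calls no one a success. Step 6 shows that the loss has another source.
- **The relative risk is biased by baseline case mix.** Under the model, a chance difference of 10 points or more in the share above the cut-off occurs in 26-38% of trials. Given 15 points or more, the χ² false-positive rate is 5-12% against 4-8% adjusted. Those are rates in selected trials; over all trials it is about 5%.
- **The primary outcome is affected by the mixing.** Entry requires PTSD symptoms on the same instrument, so hardly any woman starts without that problem. The one reservation is that the entry wording might admit less than the full diagnosis.
- **The comparison should be restricted to women with the problem at pretreatment.** This drops randomised women and hides new onset. In a separate model with fixed rates of persistence and equal new onset in both arms, restriction gained 0-21 points. With new onset of 30 v 10%, it lost about 1-20 points at 45 per arm and 3-17 at 31. Its benefit depends on treatment doing nothing for women below the cut-off.

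**Conclusion.** The point holds as a minor inefficiency in a secondary analysis. The between-arm comparisons on cut-offs are valid, but they leave unused a covariate that the plan collects and already applies to the same scales. Under the assumptions in step 2, using it is worth about 5-17 points of power. The article gives no correlation, baseline share, improvement or binary effect, so this is an illustration and not a property of the trial. The planned Holm correction would lower all the power figures. The mixing of recovered women with women who were never above the cut-off is a problem of interpretation, and it is confined to secondary scales without an entry minimum.

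**What to change.** For each outcome with a cut-off, and at each visit, replace the χ² test and raw relative risk by one prespecified regression in all randomised women. The outcome is being above the cut-off at that visit. The terms are arm and the continuous pretreatment score of the same scale. Modified Poisson regression with robust variance keeps a relative risk; logistic regression gives an odds ratio and is the model to which the power figures above apply. Apply the Holm-Bonferroni step as already planned.

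The proportion recovered among women above the cut-off at pretreatment may be reported by arm as a descriptive supplement, alongside new onset among the others. It should not replace the comparison in all women.

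The cost is a few lines of analysis wording, with no new data, visits or participants. The downsides are that a model replaces a 2×2 table, and that test size can be slightly off at 31-45 women per arm.
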